##### Long-term effectiveness

Participants who will be weekly AR responders for at least six of the 12 weeks during the follow-up period will be considered long-term effectiveness responders [23].

##### Individual symptoms

Throughout the whole study period, patients must record their IBS symptoms on paper diary cards every night before going to sleep. Diaries recorded in the run-in and treatment periods will be used to assess the efficacy and safety of the treatment, while diaries recorded during the follow-up period will be used to avoid potential bias from symptom recall. Individual symptoms are to be recorded as follows: severity of abdominal pain, abdominal discomfort, and abdominal distension evaluated by a 5-point Likert scale (0 = none; 1 = mild; 2 = moderate; 3 = severe; and 4 = intolerable); stool frequency; stool consistency classified by using the Bristol Stool Form Scale (BSFS) [24]; feelings of incomplete evacuation, urgency, and mucus evaluated on a binary scale (0 = absent; 1 = present).

##### Other outcomes

Other outcomes include the scores of the Irritable Bowel Syndromes Symptom Severity Score (IBS-SSS), Irritable Bowel Syndrome-Quality of Life Questionnaire (IBS-QOL), and Hospital Anxiety and Depression Scale (HADS) [25–27]. The questionnaire and scales above will be completed at the run-in period baseline (week 0), the end of the treatment period (week 4), and during the follow-up period (weeks 8, 12, and 16).

### Safety assessments

All participants must undergo an electrocardiogram examination and a series of clinical laboratory tests before and after the treatment (weeks 0 and 4). These will include routine blood, urine, stool, and stool occult blood, kidney function, and liver function tests. More attention will be given to the abnormal changes found in the examinations and, when necessary, a re-examination and a causality assessment will be required.

No reports of harm to patients exist from long-term clinical observations with TCKM granule treatment. Nevertheless, participants will still be instructed to report any adverse events (AEs) during the trial. The clinicians will be in charge of managing AEs. An independent Data and Safety Monitoring Board (DSMB) from GPHCM will be in charge of studying each case individually to access any serious adverse event (SAE) and the causality between the SAE and the intervention. AE details including clinical manifestations, severity, occurrence time, recovery time, management and causality will be recorded on CRFs. If any SAE occurs, it must be reported to the principal investigator, DSMB, and the Ethics Committee within 24 h, and any necessary treatment will be provided as soon as possible. When necessary, the blinding will be broken and participants will be provided suitable treatments. All SAEs will be followed up until they have been resolved.

### Data management and quality assurance

Before the conduction of the clinical trial, all investigators and relevant staff including clinicians, research assistants, and drug managers will be uniformly trained regarding the trial-specific process. The training will be conducted by the principal investigator, and a study protocol and standard operation procedure documents will be provided. This will ensure consistency among researchers undertaking the same tasks, and ensure that their actions remain in strict accordance with the study protocol. Data collection for this trial will be performed by investigators and research assistants. All collected data will be checked regularly by the data management personnel, and be overseen by monitors from the Guangdong International Clinical Research Center of Chinese Medicine (Guangzhou, China). Double data entry of CRFs will be conducted by two experienced independent data entry clerks. At the time of analysis, outliers in the resulting spreadsheets will be checked to eliminate errors in data entry. All information collected in this trial will be kept in strict confidence, and only authorized staff will have access to the trial data.

Considering that those IBS patients accompanied with psychological symptoms are more likely to withdraw, measures will be taken to facilitate maximization of their compliance. For example, before every visit, a research assistant will contact the patient to confirm the schedule; specialized telephones for this trial will be installed, in order for patients to conveniently contact clinicians or other staff. However, if patients withdraw from the trial, outcome assessment, the last date of patients taking medication, and the reasons for withdrawal will be recorded as soon as possible. We will also take some measures to monitor the drug intake by participants. For example, the participants will be required to record a symptom diary and answer the question: “Did you take the *Tiao-Chang Ke-Min granules* today?” before going to bed every day. Besides, the research assistants will ask the participants “How many packages of the granules have you taken in the past week?” weekly during the treatment period and complete the CRF.

### Sample size calculation

The sample size for this trial was calculated based on the primary outcome—the proportion of responders of AR, using PASS 11.0 software (NCSS, LLC, Kaysville, UT, USA). Combining our previous observational study with similar studies [28, 29], we assume that the proportion of responders of AR in TCKM granule group will be 60%, and in the placebo group 30%. Fifty-seven patients in each group can achieve 90% power and rule out type I error of 5% by using a two-sided test. We expect that 20% of the participants may be lost to follow-up. Therefore, the sample size in each group should be adjusted to 72. In total, 144 participants will be enrolled in this trial.

### Design of outcome predictive factors

Outcome predictive factors have been investigated by a series of qualitative methods, including academic literature research, questionnaire survey, and expert consensus conference. Predictive factors were collected mainly around three cores and four levels. The three cores refer to causative and risk factors of an illness, state of an illness, and different classification conventions from both Western medicine and CM. The four levels include demographic characteristics, clinical characteristics, systems biology characteristics, and classification assessments along multiple dimensions. These factors will be embedded in this trial for further observation and analysis. Factors that may predict successful outcome from the treatment will be selected.

### Statistical analysis

Statistical analysis will be performed by blinded specialized statisticians using PASW Statistics 18.0 (IBM SPSS Inc., Armonk, NY, USA) and SAS 9.2 software (SAS Institute Inc., Cary, NC, USA). A level of 5% (two-sided) type I error will be considered as statistically significant. Analysis will be based on both intention-to-treat and per-protocol populations.

Baseline characteristics, which also include predictive factors, will be presented for each group. From baseline to each time point, discrete variables will be described with frequencies and percentages, and continuous variables will be described with either mean and standard deviation for data with normal distribution or median and interquartile range for non-normally distributed data. For comparisons between experiment and control group at each time point, a chi-square test or Fisher’s exact test will be used for discrete variables, and the Student’s *t* test or Wilcoxon-Mann-Whitney *U* test will be used for continuous variables.

The analyses of predictive factors will be performed in two steps as follows: The first step is univariate analysis. The AR post-treatment (week 4) and follow-up (week 16) responder rates will be used as dependent variables, and predict factors, such as demographic and clinical characteristics, and key elements of CM patterns, will be used as independent variables. A logistic regression analysis will be conducted. The selection criteria for the independent variable is defined as α = 0.1. The second step is multivariate analysis. Those predictive factors selected through the first step will be entered into two multiple regression models, taking the post-treatment (week 4) and the follow-up (week 16) AR responder rates as the dependent variable. Each model will be conducted to adjust or unadjust for initial baseline level including scores of IBS-SSS, IBS-QOL, and HADS.

We plan to do some sensitivity analyses. Firstly, we will compare the primary and safety outcomes between all randomized patients and unmasking patients. Secondly, we will test the impact of the missing data on our primary outcome. The method of multiple imputations will be used to handle missing data. We will compare the results of primary outcome using the multiple imputed dataset and un-imputed dataset to test robustness.

Planned subgroup analyses will be carried out in relation to the primary outcome—AR. The main analysis for each subgroup will be an unadjusted test of interaction in a logistic model.

The following status at baseline will be applied for subgroup analyses:Demographic characteristicsDisease characteristicsClinical symptomsKey elements of CM patterns

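### The between-arm comparisons of IBS-SSS, IBS-QOL and HADS leave out the week-0 scores the trial already collects, which costs precision on these secondary outcomes

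*Protocol article*

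**What the plan says.** The section Other outcomes lists three scales, IBS-SSS, IBS-QOL and HADS, as the last group of secondary outcomes. They "will be completed at the run-in period baseline (week 0") and again at "the end of the treatment period (week 4), and during the follow-up period (weeks 8, 12, and 16"). That is one baseline and four later measurements per scale.

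The Statistical analysis section names the tests. "For comparisons between experiment and control group at each time point", a chi-square or Fisher's exact test serves discrete variables, and "the Student’s *t* test or Wilcoxon-Mann-Whitney *U* test will be used for continuous variables". The overall level is 5%, two-sided. No lead visit is named for the scales.

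The baseline scores do appear as covariates, but elsewhere. In the predictive-factor regressions, "Each model will be conducted to adjust or unadjust for initial baseline level including scores of IBS-SSS, IBS-QOL, and HADS". The dependent variable there is response on adequate relief (AR), not the scale itself.

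**The concern.** A patient's score at week 4 or later usually depends partly on where that patient started. A test that ignores the starting score counts this predictable variation as noise. It also leaves any chance imbalance in baseline severity inside the estimated treatment difference. The trial bears the cost of collecting the week-0 scores and then does not use them in the comparisons where they would help most.

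The test is stated in the protocol, so this is a weak choice and not a detail left to an unseen analysis plan. It matters because the trial is sized only for AR. Nothing in the document shows what power the scales have, so avoidable loss of precision should be avoided. Four separate visits per scale with none marked as leading also leave room to stress whichever visit looks best.

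**Working it through.** **The plan's own figure.** The only calculation in the document is for AR: 60% against 30%, 90% power, two-sided 5%. With pooled variance, n = [1.960 × √(2 × 0.45 × 0.55) + 1.282 × √(0.24 + 0.21)]² / 0.30² = 55.7, so 56 per arm. The plan states 57, and power at 57 is 90.7%. Then 57 / 0.80 = 71.25, so 72 per arm and 144 in total. The figure reproduces, and this point does not affect it.

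**Inputs for the scales.** From the document: three scales, four post-baseline visits, 1:1 allocation, 57 analysed per arm. Not in the document: the correlation r between the week-0 score and a later score. It is assumed to lie between 0.3 and 0.7.

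**Formulas.** With equal arms of size n and outcome standard deviation σ, the unadjusted difference has variance 2σ²/n. Adjusted for baseline by ANCOVA, it is 2σ²(1 − r²)/n. The variance ratio is therefore 1 − r², the interval width changes by √(1 − r²), and the equivalent unadjusted sample is n / (1 − r²). A comparison with 80% power unadjusted moves to Φ[(1.960 + 0.842) / √(1 − r²) − 1.960].

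| r (assumed) | Variance ratio | Interval width ratio | 57 per arm adjusted equals, unadjusted | 80% power becomes |
|---|---|---|---|---|
| 0.3 | 0.91 | 0.95 | 63 | 83.6% |
| 0.5 | 0.75 | 0.87 | 76 | 89.9% |
| 0.7 | 0.51 | 0.71 | 112 | 97.5% |

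These ratios refer to the t test. They do not carry over exactly to the rank test, but that test ignores baseline as well.

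**Would testing change scores escape the point?** The section speaks of change over time only for the descriptive summaries and does not name change as the tested variable. If it were tested, its variance relative to the raw later score would be 2(1 − r): 1.40, 1.00 and 0.60 at r = 0.3, 0.5 and 0.7. ANCOVA relative to change is (1 − r²) / [2(1 − r)] = (1 + r)/2: 0.65, 0.75 and 0.85. ANCOVA is the more precise in all three cases.

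**Number of comparisons.** 3 scales × 4 visits = 12. Naming one lead visit per scale leaves 3 × 1 = 3.

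**The case against.** The strongest reply is that this concerns efficiency and is not an error. With randomisation and complete data the unadjusted test is unbiased and keeps its 5% level. The scales are secondary, and the trial's main conclusion rests on AR. All of that stands, and it limits the weight of the point.

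The size of the gain is also uncertain. Entry requires IBS-SSS above 75 and excludes patients above set anxiety and depression scores. A narrowed baseline range tends to lower r, particularly for HADS, so the bottom row of the table is the less likely one. At low r the gain is small.

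A reader might draw two stronger conclusions, and the document supports neither.

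- **That the later visits use only patients still present, and so assume loss completely at random.** The article does not say how missing scale scores are handled. It names intention-to-treat and per-protocol populations, plans an outcome assessment at withdrawal, and mentions multiple imputation, most naturally for the primary outcome. The expected 20% loss is given without timing. The missing-data method for the scales is open here, not fixed badly.
- **That twelve tests at 5% carry a 46% chance of a false positive.** 1 − 0.95¹² = 0.46 requires independent tests, whereas scores within a patient are correlated. Simulation with assumed correlations of 0.5 to 0.8 between visits and 0.3 to 0.6 between scales gives about 25% to 38%. These are secondary outcomes with no stated confirmatory claim, so this affects how they are read and not the primary type I error.

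**Conclusion.** The point holds as a worthwhile improvement to a stated method. The comparisons of IBS-SSS, IBS-QOL and HADS ignore a baseline that is already collected. Under the assumed r of 0.3 to 0.7, leaving it out means that 9% to 49% of the variance could have been removed and was not. The true figure depends on an r the document does not give. The absence of a lead visit is a lesser, related weakness.

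The document does not support calling the planned comparisons biased or invalid, and nothing here touches the AR analysis or the sample size.

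**What to change.** For the three scales, replace the per-visit tests with a baseline-adjusted model. ANCOVA at each visit would do. A mixed model for repeated measures is preferable, with arm, visit, arm-by-visit, baseline score, baseline-by-visit and site. Site belongs in it because randomisation is stratified by site. The mixed model also keeps patients with partial follow-up, and is valid if data are missing at random. That assumption is useful here because the article itself expects patients with psychological symptoms to withdraw more often.

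Name one lead time point per scale in advance and label the other visits supportive. The sponsor should choose it to fit the objective: the first objective gives special weight to relapse, so the end of treatment is not the automatic choice. The reduction from 12 contrasts to 3 comes from naming the visit, not from the model. Three lead tests at 5% still carry 1 − 0.95³ = 14% if independent, so report them as secondary.

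For the diary, adjust continuous measures such as stool frequency for their run-in mean. Use an ordinal model for the graded items and a binary model for incomplete evacuation, urgency and mucus. A Gaussian model does not suit those items.

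The cost is analysis wording and some extra programming in SAS, which the plan already names. No added visits, patients or measurements are needed, and the article reports recruitment as still in preparation.

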## Methods/design

### Design

This is a parallel-group, double-blind, randomized, placebo-controlled trial. The trial will include three periods: a 1-week run-in period, a 4-week treatment period, and a 12-week follow-up period. During the run-in period, patients who fulfill the screening criteria will record a symptom diary every day, and stop taking any drugs that the trial forbids. Those, who record all items in the symptom diary for at least 5 days during the run-in period and remain eligible will be randomized at a ratio of 1:1 into either the TCKM granule group or the placebo group. Visits will be scheduled at weeks 0–16 (or at discontinuation) to assess treatment efficacy, recurrence of IBS symptoms, and occurrence of adverse events. Additionally, comprehensive predictive factors associated with patient and illness characteristics have been collected through a series of qualitative methods. These factors will be embedded in this trial for further identification. (See Figs. 1 and 2). The protocol design is based on the Standard Protocol Items: Recommendations for Interventional Trials (SPIRIT) Checklist (Additional file 1).

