#### Secondary outcomes

##### Relief and relapse incidents

The definition of relapse is the recurrence of abdominal pain/discomfort or diarrhea in IBS patients who have achieved treatment success. Achieving treatment success means that IBS symptoms have been relieved, and the relief has lasted at least 1 week after treatment. Relief and relapse incident outcomes include time until relief, time until first relapse, and total relapse times. Time until relief is defined as the time from patients receiving treatment to achieving treatment success. Time until first relapse is defined as the time from patients achieving treatment success to the recurrence of abdominal pain/discomfort or diarrhea. Total relapse times refer to the sum of relapse times during both the treatment period and the follow-up period.

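### Time until relief and time until first relapse are censored outcomes, but the only stated test that fits a duration is the t test or Wilcoxon-Mann-Whitney, with no censoring rule

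*Protocol article*

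**What the plan says.** Under Relief and relapse incidents, the protocol article defines two event times: "Time until relief is defined as the time from patients receiving treatment to achieving treatment success", and "Time until first relapse is defined as the time from patients achieving treatment success to the recurrence of abdominal pain/discomfort or diarrhea". The first exists only for patients who reach treatment success. The second exists only for those who succeed and then relapse. The Design section fixes the calendar as "a 1-week run-in period, a 4-week treatment period, and a 12-week follow-up period", so observation stops at a set point, and the Sample size calculation adds: "We expect that 20% of the participants may be lost to follow-up".

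The Statistical analysis section gives one rule for comparing the groups. Categorical outcomes go to a chi-square or Fisher test. For measured quantities the rule reads: "the Student’s *t* test or Wilcoxon-Mann-Whitney *U* test will be used for continuous variables". Logistic regression appears only for the predictive factors and for subgroup interactions on adequate relief. No Kaplan-Meier, log-rank or Cox analysis is named, and no value or censoring date is given for a patient without the event. The missing-data sensitivity analysis, with multiple imputation, concerns the primary outcome only.

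**The concern.** A duration is neither a count nor a category, so of the two halves of the stated rule only the continuous one fits. The t test and the Wilcoxon-Mann-Whitney test need a number for every patient analysed, and these outcomes supply none for patients without the event. The analyst must fill the gap with a choice that the plan does not make:

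- **Drop patients without the event.** The comparison is then between subsets selected by outcome. If the treatment works, different fractions of the two arms are dropped, and the information on who had the event at all is lost.
- **Enter the censoring time as an event time.** Everyone stays in, but a patient lost in week 1 without relief counts as relieved in week 1.

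Relapse reduction is singled out in the first trial objective, and the Discussion presents these times as part of the trial's new approach to relapse. Two of the three relief and relapse outcomes are affected.

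**Working it through.** **1. The plan's own figure.** With 60% v 30% responders, two-sided 5% and 90% power, the pooled two-proportion formula is n = [1.96·√(2·0.45·0.55) + 1.2816·√(0.6·0.4 + 0.3·0.7)]² / 0.30² = 55.7, so 56 per group. The plan states 57, at which power is 90.7%. Allowing for loss, 57/0.8 = 71.25, so 72. The sample size reproduces, and nothing below touches it.

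**2. Inputs for an illustration.**
- From the protocol: 72 per arm, 60% v 30%, 20% loss, 4 weeks of treatment and 12 of follow-up.
- Assumed, not in the protocol: exponential times; the adequate relief rates used in place of the rate of treatment success by week 4; loss spread evenly in hazard over the 4 weeks.

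**3. Time until relief, observed to week 4.**
- Hazards per week: TCKM −ln(0.4)/4 = 0.229; placebo −ln(0.7)/4 = 0.0892; ratio 2.57.
- No relief time by week 4: 0.4 × 72 = 28.8 TCKM and 0.7 × 72 = 50.4 placebo patients.
- Mean time among the relieved is 1/λ − T·e^(−λT)/(1 − e^(−λT)). With T = 4 this is 1.70 v 1.88 weeks. A 2.57-fold difference in hazard shrinks to 0.18 weeks, because the effect lies mostly in who is relieved.
- Simulated power (2,000 trials, times in days; repeat runs agree within about two percentage points):

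| Analysis | No loss | 20% loss |
|---|---|---|
| t test, events only | 9% | 9% |
| Wilcoxon, events only | 9% | 8% |
| Wilcoxon, censoring times as event times | 95% | 82–84% |
| Wilcoxon, worst rank for patients without the event | 96% | 94% |
| Log-rank | 96% | 95% |

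As a check, the Schoenfeld formula with 72 × 0.6 + 72 × 0.3 = 64.8 events gives Φ(√(64.8/4)·ln 2.57 − 1.96) = 97%.

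**4. The same hazards, observed to week 16.** Without relief: 0.4⁴ = 2.6% v 0.7⁴ = 24.0%. Mean time among the relieved, from the formula above with T = 16: 3.95 v 6.16 weeks. The events-only t test now has about 86% power, against over 99% for log-rank.

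**5. Time until first relapse.** The documents give no relapse rate, so no size is put on this outcome. The structure is enough. Time at risk starts at success and so differs between patients, and the outcome exists only in patients who succeeded. Under the assumption in step 2 those would be about 43 v 22 patients.

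**The case against.** **The rule may not be meant for these outcomes.** It is framed as a comparison at each time point, whereas these outcomes give one value per patient and the section never names them. A condensed article may leave their method to a fuller document. This is a fair reading, and a fuller plan may name a survival method. But the article states a single between-group rule without exceptions, and the continuous half is the only part a duration can fall under. As published, it points to an unsuitable test.

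**A reader might infer that the stated tests cannot use patients without the event and have almost no power.** The documents do not support that. The 9% arises only if patients without the event are dropped and relief stops being counted at week 4. The protocol states neither. Its definition of time until relief carries no week-4 limit, and diaries run throughout the study. Wilcoxon with censoring times entered as events, or with worst ranks, comes close to log-rank when nobody is lost.

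**A reader might also take 60% and 30% as the plan's own relief rates.** They are adequate relief responder rates, requiring at least two positive answers in 4 weeks. Treatment success requires relief lasting at least 1 week, which is a different event.

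**A log-rank test does not fully rescue time until first relapse.** It would compare patients selected by success after randomisation. This stands, and the fix must say so.

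**Conclusion.** The point holds. Two right-censored secondary outcomes fall under a rule for complete continuous data, and nothing says what to do with patients who have no event. The size depends on that unstated choice. In the scenario assumed above, power for time until relief runs from about 9% (events only, week 4) to about 95% (Wilcoxon with censoring times as events, no loss), falling to about 84% with 20% loss, against about 95% for log-rank. Followed to week 16, it is about 86% on events only against over 99%. These figures show how much is left open; they do not predict this trial's power.

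This is a should-fix. It concerns outcomes tied to the first objective, but only secondary ones. It would be wrong to infer that the primary analysis or the sample size is in doubt.

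**What to change.** - Exclude both outcomes from the t test and Wilcoxon rule.
- **Time until relief:** analyse all randomised patients by Kaplan-Meier, with a log-rank test stratified by site (the randomisation stratum) or a Cox model. Censor at the last diary or at the end of an observation window that the plan states (week 4 or week 16).
- **Time until first relapse:** use the same methods, counted from treatment success and censored at week 16 or the last diary. State that the analysis is restricted to patients who achieved success, is therefore not a randomised comparison, and is read as supportive.

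The cost is two or three sentences. The daily diaries already supply the dates, the named software runs these analyses, and no extra data or patients are needed. The article reports that recruitment was still in preparation, so at that stage the change could precede any outcome data.

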### Trial purpose

The specific objectives of this trial are as follows:To assess the efficacy and safety of TCKM granules for IBS, especially in reducing IBS symptom relapseTo investigate what patient and illness characteristics may predict a successful outcome from the treatment of TCKM granules, and optimize the indication.

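### The predictive-factor models have no treatment term or treatment-by-factor interaction, so they cannot separate predictors of benefit from TCKM from prognostic or chance factors

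*Protocol article*

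**What the plan says.** Under Trial purpose, the second objective is to "investigate what patient and illness characteristics may predict a successful outcome from the treatment of TCKM granules" and to use the answer to refine the indication.

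Under Statistical analysis, the route to that answer has two steps:

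- **Step 1, univariate logistic regression.** The dependent variables are AR response after treatment (week 4) and at follow-up (week 16). On the other side of the model, "predict factors, such as demographic and clinical characteristics, and key elements of CM patterns, will be used as independent variables". "The selection criteria for the independent variable is defined as" α = 0.1.
- **Step 2, multivariable regression.** The factors that pass step 1 enter one model per outcome, with and without adjustment for baseline IBS-SSS, IBS-QOL and HADS scores.

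Treatment arm appears in neither step. The text does not say whether the models use both arms or TCKM patients only.

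A separate paragraph at the end of the same section plans subgroup analyses of the primary outcome by demographic characteristics, disease characteristics, clinical symptoms and elements of CM patterns: "The main analysis for each subgroup will be an unadjusted test of interaction in a logistic model".

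**The concern.** Who responds and who benefits from TCKM are different questions. A factor that raises the chance of response equally on TCKM and on placebo is prognostic and gives no reason to prefer TCKM in those patients. A factor is predictive of benefit only if the TCKM-placebo difference changes with it, and only a comparison across the randomised arms shows that.

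The two-step models make no such comparison. If the arms are pooled without a treatment term, the factor coefficient averages its association over TCKM and placebo patients. If only TCKM patients are used, the coefficient mixes prognosis with effect modification. A treatment main effect alone would not help either, because the interaction carries the information. An indication drawn from these models could therefore steer TCKM towards patients who would have improved on placebo.

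**Working it through.** **1. The plan's own figures.** The Sample size calculation section assumes AR response of 60% on TCKM and 30% on placebo, and states: "Fifty-seven patients in each group can achieve 90% power and rule out type I error of 5% by using a two-sided test". With pooled variance:

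n = [1.960 × √(2 × 0.45 × 0.55) + 1.2816 × √(0.6 × 0.4 + 0.3 × 0.7)]² / 0.3² = (1.379 + 0.860)² / 0.09 ≈ 55.7, so 56 per group.

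The stated 57 is one higher and gives 90.7% power. Allowing for 20% loss, 57 / 0.8 = 71.25, so 72 per group and 144 in total. These figures reproduce and are not in dispute. They set the range used below: 57 per arm (after the expected loss) to 72 per arm (no loss).

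**2. Set-up.** The following are assumptions, not in the protocol: a binary factor present in half of each arm, and the effect sizes in the table. Overall response is held at 60% and 30% throughout. For r responders among n patients, L = ln[(r + 0.5)/(n − r + 0.5)] and V = 1/(r + 0.5) + 1/(n − r + 0.5). Subscripts T and C are TCKM and placebo; 1 and 0 are factor present and absent.

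- Screen, pooled or TCKM-only: z = (L₁ − L₀)/√(V₁ + V₀).
- Interaction: z = [(L_T1 − L_T0) − (L_C1 − L_C0)]/√(V_T1 + V_T0 + V_C1 + V_C0).

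**3. Results.** Percentage of 200,000 simulated trials that flag the factor, at 57 / 72 per arm:

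| Factor (response if absent → present) | Pooled screen, 0.1 | TCKM-only screen, 0.1 | Interaction, 0.1 | Interaction, 0.05 |
|---|---|---|---|---|
| Null | 9.3 / 9.5 | 10.4 / 9.8 | 9.8 / 9.7 | 4.5 / 4.6 |
| Prognostic, OR 2 (TCKM 52→68%, placebo 23→37%) | 51.6 / 61.3 | 37.4 / 41.2 | 9.5 / 9.5 | 4.5 / 4.6 |
| Prognostic, OR 2.5 (49→71%, 21→39%) | 72.3 / 81.7 | 53.3 / 59.2 | 9.3 / 9.4 | 4.3 / 4.6 |
| Prognostic, OR 3 (47→73%, 19→41%) | 84.8 / 91.9 | 65.7 / 72.4 | 9.2 / 9.3 | 4.2 / 4.5 |
| Moderate modifier (45→75%, 30→30%) | 49.8 / 59.4 | 77.6 / 84.0 | 47.8 / 55.9 | 35.4 / 43.2 |
| Crossover modifier (45→75%, 45→15%) | 7.6 / 7.8 | 77.5 / 84.2 | 96.5 / 98.8 | 92.9 / 97.2 |

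Letting the factor's split vary at random around one half lowers the prognostic ranges by at most about 4 points: 50% to 89% pooled and 34% to 71% TCKM-only.

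**4. Reading the table.** A purely prognostic factor passes the planned screen far more often than the nominal 10%, in either population. The interaction test holds its nominal rate.

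The last row shows the opposite failure. The TCKM effect is 45 − 45 = 0 points without the factor and 75 − 15 = 60 points with it. Pooled response is (45 + 45)/2 = 45% without it and (75 + 15)/2 = 45% with it. The pooled screen sees no association and passes the factor no more often than a null one. This is an extreme case, chosen to show the mechanism.

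**5. Chance selection.** The number of candidate factors is not given. If 20, 30 or 50 are independent and null, step 1 passes 0.1 × 20 = 2, 0.1 × 30 = 3 or 0.1 × 50 = 5 on average per outcome. The probability of at least one is 1 − 0.9^k = 88%, 96% or over 99%. These are counts after step 1 only. If step 2 is then judged at 5%, about 0.9 to 1.0, 1.2 to 1.5 and 2.0 to 2.2 remain.

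**The case against.** The best defence is that the protocol does plan to test effect modification. The subgroup paragraph uses interaction tests on AR, and its baseline domains largely match the factors named for the two-step models. A reader might infer from the two-step models that the trial never uses its placebo arm for this question, or cannot address its second objective at all. The document does not support either inference. What remains is that those tests cover the primary outcome only, so week 16 has none, and nothing links them to the selection of predictive factors.

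A reader might also infer that the models would pick up only prognostic or chance factors. That is too strong: in TCKM patients alone, both modifiers in the table pass in 78% to 84% of trials. The fault is that they cannot be told apart from prognostic factors once selected.

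The article is condensed, and its list of independent variables is introduced as examples, so an unmentioned treatment term is conceivable. Against that, every example is a patient characteristic, and the adjustment set named for step 2 also omits treatment. The absence of internal validation and of a factor count is different: a full protocol or analysis plan may well supply these, and neither is counted here.

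Finally, step 2 includes a version adjusted for baseline severity, quality of life and anxiety/depression. That deals in part with severity as a prognostic factor, but not with other prognostic factors, and it creates no comparison between arms.

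**Conclusion.** The concern holds for the two-step predictive-factor models. As described, they cannot distinguish factors that predict benefit from TCKM from purely prognostic or chance factors, so they do not support a refined indication under the second objective.

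The size depends on assumptions: 50% prevalence, odds ratios of 2 to 3, the planned response rates, and 57 to 72 patients per arm. Prognostic factors then pass in about 52% to 92% of trials pooled and 37% to 72% TCKM-only. The conclusion itself needs none of these figures, because it follows from the missing interaction term. The primary AR comparison and the sample size are unaffected.

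**What to change.** In Statistical analysis:

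- Fit the predictive-factor models in all randomised patients, with treatment, factor and treatment-by-factor terms, for both week 4 and week 16.
- Call a factor predictive of benefit from TCKM only on its interaction, reported with a confidence interval. Label main effects prognostic.
- State how these models relate to the planned subgroup interaction tests, so that the two do not yield separate lists.
- State that any resulting indication is exploratory. Interaction tests also produce chance findings: with 20 null factors tested at 5%, 0.05 × 20 = 1 is expected per outcome.

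The cost is analysis text and some programming. No new data are needed, the placebo arm is already randomised 1:1, and the article reports recruitment as still in preparation, so the change can be pre-specified.

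The downside is that fewer factors will be declared predictive. Under the assumed moderate modifier, with a TCKM effect of 15 points (45 − 30) without the factor and 45 points (75 − 30) with it, power at the 5% level is only about 35% to 43%. That supports the exploratory label; it does not justify keeping a model that leaves the question untested.
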